## Abstract

**Background:**

There is a large unused potential for risk reduction in the preoperative period via effective lifestyle intervention targeting co-existing risky lifestyles: Smoking, malNutrition, obesity, risky Alcohol intake and insufficient Physical activity (SNAP).

This trial compares the efficacy of the integrated STRONG programme with standard care on preoperative risk reduction and secondly on SNAP factor improvement and frailty, postoperative complications and quality of life. A nested interview study explores the patient preferences and the multi-perspective view of patients, relatives and health professionals.

**Methods:**

In total, 42 surgical patients with ≥1 SNAP factor are allocated to individually tailored STRONG programme or usual care during adjuvant chemotherapy prior to radical bladder cancer surgery. The STRONG programme has ≥6 weekly sessions with patient education, motivational and pharmaceutical support. It is based on intensive smoking and alcohol cessation interventions reporting perioperative quit rates > 50%.

Surgical risk reduction is measured as ≥1 step for 1 or more risky lifestyles on the ASA-score, secondly as having no risky SNAP factors, and as any SNAP improvement. The outcomes are validated by measurements and biomarkers. Postoperative complications are categorised according to the Clavien-Dindo classification. Health-related quality of life is measured by EQ-5D.

The patients are followed up after 6 weeks at surgery and 6 weeks and 6 months postoperatively.

A representative sample of the participants, their relatives and the clinical staff are interviewed until data saturation. Transcription, triangulated analyses and data management are conducted using NVivo computer software.

**Discussion:**

The surgical agenda is characterised by fixed dates for surgery focusing on clear risk reduction within a short time. This requires a clinical useful lifestyle intervention programme with a high effect and coverage as well as containing all SNAP factors and tailored to individual needs.

The STRONG programme seems to meet these requirements. After development in multi-professional collaboration, STRONG is delivered by a specially trained nurse as part of the surgical patient journey.

Overall, this study will bring important new knowledge about risk reduction in a frail patient group undergoing major cancer surgery.

**Trial registration:**

Registration at www.clintrials.gov (NCT04088968)

The manuscript form from https://trialsjournal.biomedcentral.com/bmc/journal and the SPIRIT guidelines are followed.

## Administrative information

Note: the numbers in curly brackets in this protocol refer to SPIRIT checklist item numbers. The order of the items has been modified to group similar items (see http://www.equator-network.org/reporting-guidelines/spirit-2013-statement-defining-standard-protocol-items-for-clinical-trials/).

## Introduction

### Background and rationale {6a}

#### The problem to be solved

Surgery remains the gold standard of treatment for many diseases, but the outcomes are poor among frail patients with unhealthy lifestyles; thus, strategies to optimise the patient group are increasingly important [1–7]. The improved intraoperative techniques and enhanced recovery after surgery (ERAS), e.g. the ERAS protocol, are important [8]. However, there is a large unused potential of risk reduction in the preoperative period [9], in particular the modifiable risk factors, which can be targeted with preventive strategies [10].

Even in case of screening for smoking, nutrition, alcohol and physical activity (SNAP) at surgery, screening results are only fragmentally followed up by systematic interventions in the clinical pathways for patients with cancer and other diseases [11]. This is despite the World Health Organization (WHO) recommendations and the surgical guidelines endorsing all patients to be offered evidence-based support for risk reduction. In 2014, the American Society for Anesthesiologists (ASA) included relevant details on alcohol, smoking and obesity in the international preoperative risk evaluation for adults, the ASA-score [12].

The SNAP factors often co-exist and each add to the surgical risk [13–15]: about 50% for daily smoking, alcohol > 2 drinks/day [16] and severe malnutrition — similar to the risks related to severe cardiac, pulmonary and kidney insufficiency. Obesity even at cancer surgery [17–19] and low physical activity are followed by 10–20% increase [20]. Frailty is an example of co-existing SNAP factors with a major impact on the surgical outcome [21, 22].

#### Pathophysiological mechanisms

Patients with an unhealthy lifestyle develop the same type of complications as all other patients, just more frequently [23–26]^.^ The pathophysiology involves a comprehensive suppression of several organ systems of importance for surgical outcomes. They dysfunction prior to surgery and add to the surgical trauma itself, targeting the same organ functions. For alcohol, the preoperative organ dysfunction even exists in patients without, e.g. alcohol-induced liver disease, and for smoking without, e.g. smoking-induced lung disease [27]. The organ damage is often subclinical and takes place at the cellular level, thus reducing the extra capacity that usually supports the patient successfully during surgery and recovery.

#### Need for a combined programme

The risk at surgery increases with co-existing risk factors, but no integrated programme exists targeting all SNAP factors [5, 20, 28]. We have shown that an intensive intervention aiming at complete smoking or alcohol abstinence for 4 to 8 weeks halves the postoperative complication rate and indicates a sustained effect for longer time [29, 30]. Preoperative inspiratory exercise for 1–2 weeks reduces postoperative pneumonia [31], while malnutrition intervention before surgery is part of the international guidelines [6, 7, 32]. General physical exercise reduces the postoperative recovery, but the impact on complications is disappointing [20, 33, 34]. Preoperative obesity and frailty interventions are still sparsely investigated in cancer surgery [18, 35–37].

Recently, our group successfully tested a combined smoking and alcohol cessation intervention [38]. We also identified a minimal impact of the social gradient after a successful intensive smoking cessation intervention [39]. In addition, the social inequality in health promotion success could be minimised through positive/selective involving procedures and support during the total intervention [40]. Our STRONG programme will build on these results.

#### The frameworks

This study integrates two frameworks:
Prehabilitation and pathophysiology/functionality improvement (Fig. 1)Lifestyle intervention as introduced by the operational model [41], and delivered as the “Gold-Standard Program” (GSP) for smoking cessation intervention [42], translated and evaluated for perioperative alcohol intervention [40] and other lifestyles and patient groups [43]

**Fig. 1 Fig1:**
[figure not shown]
Potential of preoperative improvement by intensive SNAP prehabilitation

#### Preference among patients, relatives and staff

Cancer diagnosis and surgery are considered “windows of opportunity” for a successful lifestyle change. A common staff barrier (or misconception) is “that it is unwanted by the patient” which might imply judgements. Interestingly, the patients often express a need for being involved in their own recovery, regarding perioperative lifestyle intervention as part of the surgical treatment [44, 45]. By nesting interviews of patients, relatives and staff, we will provide triangulated perspectives of preferences, and experienced facilitators and barriers for the STRONG programme.

Overall, it is necessary to develop a combined programme with a strong potential to reduce the high risk at surgery, originating from all the SNAP factors. Our STRONG programme builds on the existing evidence, including the feasibility to be delivered by specially trained nurses in the complex surgical setting.

### Objectives {7}

The main objective is to compare the efficacy of the intensive prehabilitation STRONG aiming at risk reduction with standard care for patients with at least one SNAP factor (Smoking, Nutrition – obesity and/or malnutrition - risky Alcohol drinking and low Physical activity) prior to bladder cancer surgery and secondly to compare the improvement of SNAP factors, with frailty, postoperative complications and health-related quality of life. Furthermore, we aim to explore the patient preferences as well as a multi-perspective view of the STRONG programme.

The main hypothesis is that intensive SNAP prehabilitation reduces the high surgical risk related to the five risky lifestyles compared to treatment as usual.

### Trial design {8}

This is a superiority intervention study in a randomised design with parallel groups using allocation 1:1. An interview study is nested in the trial.

## Methods: participants, interventions and outcomes

### Study setting {9}

The patients are recruited from the Department of Urology, and the intervention takes place during their preoperative chemotherapeutic treatment at the Department of Oncology, both at Copenhagen University Hospital, Rigshospitalet, Copenhagen. The intervention is performed by the surgical STRONG team anchored at the Clinical Health Promotion Centre, The Parker Institute, Bispebjerg-Frederiksberg Hospital, Part of Copenhagen University Hospitals, Denmark. A panel of patients with personal experience of cancer surgery is formed and actively involved in the research process (Fig. 2).

**Fig. 2 Fig2:**
[figure not shown]
Trial profile

### Eligibility criteria {10}

Inclusion criteria: Patients > 18 years, at least one of the five SNAP factors (defined below) and scheduled for radical cystectomy (RC) due to bladder cancer and referral to neo-adjuvant chemotherapy preoperatively
“Smoking”: daily smoking — no limitations [29]; validated by carbon monoxide (CO) in the breath test“Obesity”: BMI above 30 [46], validated by weight and height“Malnutrition”: based on ESPEN guidelines for surgery including albumin concentration in blood [6]“Risky drinking”: > 2 standard drinks per day (in average; 1 drink = 12 g ethanol), identified by timeline follow-back (TLFB) [47], and validated by alcohol biomarkers (carbohydrate-deficient transferrin (CDT), plasma phosphatidylethanol (P-Peth) and urine ethylglucuronide (U-EtG))“Physical inactivity”: < 30 min physical activity per day or 3.5 h per week

Exclusion criteria: pregnancy and breastfeeding as well as allergy and other contra-indications to pharmaceutical support, exercise or nutritional intervention; inability to give informed consent (e.g. low age, severe mental illness including delirious conditions, consciousness issues, local language challenges and similar) and withdrawal of informed consent.

### Who will take informed consent? {26a}

In connection with the initial planning of surgery, the patient’s designated urologist and a clinical project nurse approach eligible patients and invite them to participate in the study.

A project nurse will give oral and written information and answer questions. The informed consent is collected as soon as possible to allow for at least 6 weeks of prehabilitation during the preoperative oncological treatment period (about 8–12 weeks).

### Additional consent provisions for collection and use of participant data and biological specimens {26b}

During the project period, new markers may be developed, and we ask participants separately about giving informed consent for future studies.

## Interventions

### Explanation for the choice of comparators {6b}

For comparison, a control group is necessary in this study, as this is the first RCT to evaluate an intensive lifestyle intervention including up to five SNAP factors. Though theoretically possible from the literature as presented above, we do not know if and to which degree it is possible for the patients to successfully change several risky lifestyles at the same time during the perioperative period.

The patients undergoing major bladder cancer surgery are chosen because they may benefit very much from a perioperative lifestyle intervention. Smoking induces urothelial cancer, and the candidates for radical cystectomy constitute a group with a short-term high perioperative risk and a long-term health reduction. They are characterized by age around 70 years, a high comorbidity [5], about 25% at severe nutritional risk and 30% current smokers. Still, obesity is seldom seen in patients undergoing RC [48] but a one-unit increase in body mass index (BMI) has been significantly associated with a higher risk of a major complication in patients undergoing RC [19].

Overall, these patients are considered a frail population with complication rates up to 64% within 3 months, postoperatively [49, 50].

### Intervention description {11a}

The intervention group receives the intensive STRONG prehabilitation programme tailored to meet the individual patient’s need for risk reduction at surgery. It has minimum five educational sessions over 6 weeks (i.e. about one weekly), motivational support and pharmaceutical support such as nicotine replacement therapy as indicated. The education relates directly to their surgical treatment and includes introduction to STRONG, motivational level, ambivalence, pros and cons; symptoms of addiction and/or withdrawal (experience and expectations); relapse (description and management); benefits of short- and long-term lifestyle change; continued lifestyle change following STRONG, continued education based on the current conditions.

STRONG is introduced with the surgical recommendations in ‘Engage in the process of change’ [41]. The smoking follows the Gold Standard Programme (GSP) [42], which also has been translated to the standardised alcohol cessation intervention [40], exercise training programme and nutritional intervention [43].

The STRONG programme focuses on healthy days, defined as days without smoking or drinking, eating according to the nutritional plan and being physically active for at least 30 min. The number of SNAP factors involved relates to the individual patient’s unhealthy lifestyles. The content of the programme is recommended based on symptoms and chosen by the patients from a roll-down menu, e.g. type of nicotine replacement therapy (NRT), alcohol withdrawal prophylaxis, combination of food or nutritional supplement adding up to the intake needed and type of physical activity.

The control group also receives the participant information and standard care, which includes that smokers are offered a very brief advice (VBA) and referral to a municipal clinic for smoking cessation intervention.

All participants receive the national folders on smoking and alcohol advise in relation to surgery. All are free to use any support offered outside the study, including the free access to lifestyle intervention in their municipality. Patients are asked if they have experienced side effects, particularly of the pharmacological support. Potentially unknown side effects are reported and, if serious, may lead to early termination of the trial.

Clinical project nurses, who have taken part in a 5-day educational programme followed by practical training in the STRONG programme based on the GSP, provide the intervention. The daily project leader ([name]) ensures that the counsellor follows the principles of the GSP programme by discussion of the intervention regularly.

### Criteria for discontinuing or modifying allocated interventions {11b}

A participant may withdraw from the study at any time without this impacting on any future investigations and/or treatment at the site, by the project team or other staff associated with the study. The project team may discontinue any participant’s participation, e.g. due to an adverse event and safety concerns. The principal investigator has the right to terminate the study. Reasons may include unsatisfactory fulfilment of the design, participant enrolment, time schedule and administrative agreements.

### Strategies to improve adherence to interventions {11c}

The adherence is measured as meeting adherence during the intervention and follow-ups. In addition, the lifestyle changes are monitored by interviews and validated by markers.

### Relevant concomitant care permitted or prohibited during the trial {11d}

All participants are free to use any support offered outside the project, including the free access to lifestyle intervention in their municipality.

### Provisions for post-trial care {30}

In case of needs (for post-trial care and others), the participants are followed long-term at the Department of Urology and/or Department of Oncology.

### Outcomes {12}

#### Risk reduction at surgery from changes in lifestyle

Primary outcome: Number of patients with surgical risk reduction of at least 1 step for 1 or more risky lifestyles on the ASA-score [51] after 6 weeks which is the end of the intervention.

Secondly: Number of patients without their preoperative risky lifestyles at 6 weeks after inclusion, at surgery and at 6-week and 6-month follow-up postoperatively:
Successful smoking cessation, validated by CO in the breath test and U-cotinineMalnutrition: Not at risk of malnutrition (ESPEN surgical guidelines, incl. albumin concentration) [6]Obesity: body mass index (BMI) < 30 or at least 5% loss of body fat mass and max 10% for obesity at 6 weeks (0.5–1 kg/weekly and below 1% gain of body fat mass at 6 months (without developing malnutrition) [52]Successful alcohol cessation at 6 weeks and intake below risky limits at 6 months, validated by CDT, P-Peth and U-EtGPhysical activity at least 30 min per day or 3.5 h per week and 6-min walk test (6MWT) > 500 m

Number of patients with any reduction of any of their lifestyles, i.e. reduced number of cigarettes, amount of alcohol intake and body fat mass, level of malnutrition as well as increased body-muscle mass, minutes of physical activity per day and 6MWT. Number of patients with reduced frailty level, measured by Lammers definition [22].

##### Health-related quality of life

Measured by EQ-5D [53] with 5 dimensions and a visual analogue scale (VAS). This generic quality of life instrument used in clinical studies reflects the severity of five dimensions, mobility, self-care, usual activities, pain/discomfort and anxiety/depression, at three levels of severity. Each of the five dimensions is divided in five levels of perceived problems. The higher level, the more problems are experienced. Overall health is measured with a visual analog scale (VAS) from 0 to 100 with a higher score representing a better health. The questionnaire is cognitively undemanding, and it takes only a few minutes to complete. It has been found well-functioning in older age groups comparable with the population in this study protocol.

#### Postoperative complications

Postoperative complications are defined by requiring documented treatment within 30 days and 6 months after surgery, categorised in accordance with the Clavien-Dindo grading [54] as well as the Comprehensive Complication Index (CCI) [55]. They include adverse events and side effects (Table 1).

**Table 1 Tab1:** Outcome collection during the study

Outcomes	Week 6 (FU)	Surgery	Follow-up 30 days	Follow-up 3 + 6 months
Main: Risk reduction of at least 1 step for at least 1 risky lifestyle (ASA-definition)				
Yes/no	X	X	X	X
Level (going from–to)	X	X	X	X
Secondary outcomes				
Quitting the risky lifestyles (as intervened)	X	X	X	X
Any reduction in lifestyles or frailty	X	X	X	X
Hospital Anxiety and Depression Score (1Q)	X	X	X	X
General HR-Quality of life (EQ-5D)	X	X	X	X
Complications (yes/no)			X	X
Clavien-Dindo (grade) and CCI			X	X

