### Participant timeline {13}

The patients are enrolled, allocated and begin the intervention about the same date, which is at least 6 weeks prior to surgery.

The semi-structured interviews take place after ending the STRONG programme using an interview guide developed by the study team, based on the study aim, previous prehabilitation research [56] and concepts in the frameworks described above.

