### Adverse event reporting and harms {22}

Information of adverse events to the interventions is collected at every meeting and if any occur they will be reported to the Danish Medicines Agency. In addition, the participants can also contact the staff via the hotline.

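### The only outcome defined to contain adverse events counts treated events after surgery, so it misses the weeks in which STRONG is given; preoperative collection is tied to meetings, of which STRONG has more

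*Protocol article*

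**What the plan says.** Under Outcomes {12}, Postoperative complications, the outcome is defined by events "requiring documented treatment within 30 days and 6 months after surgery", graded by Clavien-Dindo and the Comprehensive Complication Index. The same paragraph adds: "They include adverse events and side effects (Table 1". Table 1 marks the complication rows at 30 days and at 3 + 6 months and leaves Week 6 and Surgery blank. No other outcome in that section or in Table 1 is said to contain adverse events.

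On timing, Participant timeline {13} says that patients "begin the intervention about the same date, which is at least 6 weeks prior to surgery". The primary outcome is taken "after 6 weeks which is the end of the intervention". Prehabilitation falls "during the preoperative oncological treatment period (about 8–12 weeks"), and Table 3 continues its assessments up to the operation.

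On collection, Adverse event reporting and harms {22} states: "Information of adverse events to the interventions is collected at every meeting", with reporting to the regulator and a hotline for participants. Intervention description {11a} says that patients are asked about side effects, without giving a schedule. Criteria for discontinuing {11b} allows the team to stop a patient's participation for an adverse event.

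On contacts, Intervention description {11a} says of STRONG: "It has minimum five educational sessions over 6 weeks (i.e. about one weekly"). The abstract gives a slightly different count: "The STRONG programme has ≥6 weekly sessions". Table 3 lists weekly assessments for the STRONG group only, described as additional to the schedule for all patients. That schedule, Table 2, is not shown.

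**The concern.** The harms that STRONG itself could cause arise mainly while it is being delivered: reactions to nicotine replacement, alcohol withdrawal or its prophylaxis, exercise injuries, and effects of dietary change in frail patients on chemotherapy. The article makes a postoperative outcome the place where adverse events and side effects are counted, and that outcome opens only once delivery is over.

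The preoperative events that are collected come from meetings, and the two arms do not have the same number of meetings. If someone later set those events side by side by arm, STRONG could appear to cause more of them partly because its patients were asked more often. At stake is a comparable account of harms during the intervention, in what the article calls the first randomised trial of an intensive programme covering up to five SNAP factors.

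**Working it through.** The plan gives no figure on this point, so there is none to reproduce. The check compares time windows and contact schedules.

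**1. Window against exposure.**
- Outcome window: opens at surgery, closes 6 months later (Postoperative complications; Table 1).
- Exposure: starts at least 6 weeks before surgery (Participant timeline {13}). It ends 6 weeks after the start according to the primary outcome; Table 3 carries assessments on until surgery.
- Overlap: 0 weeks on either reading. An event that arises and resolves before the operation has no place in the outcome.
- Minimum exposure outside the window: 21 STRONG patients (Sample size {14}) × 6 weeks = 126 patient-weeks, assuming that all 21 complete the minimum. The documents give no preoperative adverse-event rate, so this cannot be turned into a number of missed events.

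**2. Collection by arm.** {22} ties collection to meetings. Table 3 gives STRONG weekly meetings in addition to whatever both arms share. Even if Table 2 schedules an identical check in both arms, STRONG patients keep extra occasions on which an event can be noted. The direction of any difference in ascertainment is therefore clear. Its size is not.

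**3. Illustration of size, on assumptions only.** Let q be the chance that an existing event is noted at one contact, and k the number of contacts. Assume independent contacts and an event present at all of them. The chance that it is noted at all is 1 − (1 − q)^k. Take k = 6 in STRONG (five sessions, the fifth being the Week 6 contact, plus Surgery) and k = 2 in controls (Week 6 and Surgery, the only preoperative points visible in Table 1). With equal true risk, the apparent ratio of noted events is:

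| Assumed q | STRONG, k = 6 | Control, k = 2 | Ratio |
|---|---|---|---|
| 0.3 | 0.882 | 0.510 | 1.73 |
| 0.5 | 0.984 | 0.750 | 1.31 |
| 0.7 | 0.999 | 0.910 | 1.10 |

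Neither q nor the control k can be taken from the documents. More common contacts in Table 2 would move the ratio towards 1, as would use of the hotline by controls.

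**4. What an equal question could show.** With 21 patients per arm, seeing no event in one arm leaves an exact two-sided 95% upper limit of 1 − 0.025^(1/21) = 0.161, about 16%. Such data support description, not a formal comparison.

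**The case against.** The strongest reply has four parts.

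- A postoperative complication outcome should start at surgery, so blank preoperative cells are correct. That stands. The difficulty is only that this outcome is also named as the one containing adverse events and side effects.
- Preoperative harms are watched: patients are asked about side effects, events are collected at meetings and reported, and a hotline exists. The passage on side effects in {11a} may well mean both arms. All of this stands. A reader might infer that harms during STRONG go unmonitored; the text says otherwise.
- No by-arm test of preoperative events is planned. Statistical methods {20a,b,c} names risk reduction, SNAP improvement and quality of life. Asking most often where the intervention is delivered suits surveillance. This stands too, so the unequal collection matters only if such a comparison is made.
- Table 2 is missing from the text at hand and may schedule the same question for everyone. A reader might divide the visible contacts in the two arms and treat the result as the size of a bias. That does not follow: the control count is unknown, and a ratio of contacts is not a ratio of detected events.

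A reader might also infer that the postoperative comparison is distorted, or that nothing can be mended at the analysis stage. Neither is supported. Complications are registered by two assessors blinded to allocation ({18a}), at time points that Table 1 does not separate by arm. Listing meeting-only events separately is something that an analysis plan can do. Only the equal question has to be settled when data are collected.

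**Conclusion.** The point holds as a minor one. The single outcome said to contain adverse events and side effects does not overlap the period in which STRONG is given, a minimum of 126 patient-weeks under full completion. Events before surgery are collected at meetings, and STRONG has more of these, so a by-arm comparison of such events would lean towards more in STRONG. The amount cannot be determined from the documents; the ratios of 1.10 to 1.73 above are illustrative and depend on assumed detection chances and on an assumed control schedule. The conclusion about the window rests on the article's own definition and timeline and needs no assumption about Table 2. The primary outcome, the blinded complication assessment and the protection of participants are not affected.

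**What to change.** 1. In Postoperative complications, state that the outcome takes in adverse events and side effects after surgery only.
2. Add an adverse-event row to Table 1, marked at Week 6 and Surgery, with the same question put to both arms. If Table 2 already schedules this, it is enough to refer to it.
3. Base any between-arm summary of preoperative adverse events, deaths or cancelled operations on those common contacts, in all randomised patients. List events noted only at STRONG meetings separately.

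The cost is one changed sentence, one table row, one short descriptive table, and one extra question for patients and staff at two existing contacts. No visit or patient is added and the sample size is unchanged. The limitation is that 21 per arm gives descriptive precision only.
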